#### Withdrawal criteria

Participant Initiated: Participants may withdraw at any time without penalty. Reasons will be documented if provided.Investigator Initiated: The principal investigator may discontinue a participant for:Major protocol deviation (e.g., unplanned change in anesthesia or surgery).Loss to follow-up (inability to complete the 7-day primary outcome assessment).A serious perioperative complication where continuation is not in the participant's best interest.A Serious Adverse Event (SAE) probably or definitely related to the intervention.Data Handling: The primary analysis will follow the intention-to-treat (ITT) principle. Data collected until withdrawal will be included unless consent for data use is explicitly revoked.

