### Sample size estimation

The sample size calculation was based on the primary composite outcome of postoperative organ dysfunction. A previous cohort study reported incidences of 51.7% *vs*. 38.1% for standard and individualized management, respectively [15]. However, the particularly high vulnerability of older hip fracture patients is demonstrated by elevated rates of intraoperative hypotension (approximately 60%) [18], postoperative AKI (7.6% to 11.3%) [18–20], and myocardial injury (14%) [18], we anticipate a higher baseline risk in our standard care group and a potentially larger treatment effect.

Therefore, to ensure the study is adequately powered to detect a conservative and clinically significant effect, we assumed a 55% incidence of the primary outcome in the standard management group and a 30% incidence in the individualized management group. Using a chi-square test in PASS 15 software with a two-sided α of 5% and 90% power, a minimum sample size of 82 patients per group was calculated. To account for an anticipated 10% dropout rate, a total of 180 patients (90 per group) will be enrolled. This calculation employs a conservative effect size estimate, anticipating a higher baseline risk of organ dysfunction in our frail older hip fracture population compared to the referenced study in major abdominal surgery [15], thereby ensuring adequate power to detect a clinically meaningful difference.

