### Statistical analysis

All analyses will be performed using SPSS (version 25.0; IBM Corp., Armonk, NY, USA). A two-sided *P*-value < 0.05 will be considered statistically significant. The primary outcome will be compared between groups using the chi-square test. To account for potential baseline imbalances, the primary analysis will be supplemented with a multivariable logistic regression model adjusting for age (as a continuous variable) and ASA physical status classification. The normality of continuous data will be assessed using the Shapiro–Wilk test. Continuous variables will be summarized as means with standard deviations or medians with interquartile ranges and compared using the independent samples t-test or the Mann–Whitney U test, as appropriate. Categorical variables will be presented as numbers (percentages) and compared using the chi-square test or Fisher’s exact test.

For secondary analyses, the relationships between the intervention and the primary outcome will be further explored using multivariable logistic regression, adjusting for key baseline covariates. Repeated-measures data (e.g., SBP over time) will be analyzed using generalized estimating equations. Time-to-event data will be analyzed with the Kaplan–Meier method and the log-rank test. The ITT principle will be applied for all analyses. Any missing data will be handled using complete-case analysis.

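### Intention-to-treat is declared for all analyses, but complete-case handling and investigator withdrawal without stated continued follow-up can drop or misclassify randomised patients for outcome-linked reasons

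*Protocol article*

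**What the plan says.** Under Statistical analysis, two consecutive sentences set the analysis population and the missing-data rule: "The ITT principle will be applied for all analyses. Any missing data will be handled using complete-case analysis". Withdrawal criteria repeats the first part: "The primary analysis will follow the intention-to-treat (ITT) principle".

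The same section lists grounds on which the principal investigator may discontinue a participant. One is "A serious perioperative complication where continuation is not in the" participant's best interest. Another is "A Serious Adverse Event (SAE) probably or definitely related to the intervention". The other two are a major protocol deviation, such as an unplanned change of anesthesia or surgery, and being unable to complete the 7-day primary outcome assessment. On data, it says: "Data collected until withdrawal will be included unless consent for data use is explicitly revoked". It does not say whether outcome assessment continues after the investigator withdraws someone.

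Randomization and blinding has the envelope opened immediately before induction, so intraoperative and postoperative withdrawals come after randomisation. Primary outcome calls for daily assessment. Follow-up procedures provides a day-7 return visit or telephone interview for patients discharged early, and bases adjudication on all data obtained up to day 7. Sample size estimation expects losses: "To account for an anticipated 10% dropout rate", 90 per group are enrolled against a minimum of 82.

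**The concern.** For a binary outcome over a fixed 7-day window, complete-case analysis excludes every randomised patient whose outcome is missing. The two sentences under Statistical analysis are therefore compatible only if nothing is missing, and the plan expects that some data will be.

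The grounds for withdrawal make the loss hard to regard as random. The endpoint is respiratory, cardiovascular, renal or neurological dysfunction, and a serious perioperative complication may be such an event or precede one. Withdrawal for an SAE attributed to the intervention may also differ between arms, because the arms receive norepinephrine differently (continuous titrated infusion against rescue boluses).

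At stake is the primary comparison. It could be distorted by who leaves the denominator, or who is scored event-free, while still being reported as intention-to-treat.

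**Working it through.** **1. The rules applied to one patient.** Suppose the investigator withdraws a patient on day 1.
- *Organ dysfunction already recorded:* the retention sentence in Withdrawal criteria keeps the event, so the patient counts.
- *No event recorded yet:* days 2 to 7 may never be observed. The patient is dropped if Statistical analysis governs, or adjudicated on partial data as event-free if Follow-up procedures governs. The article does not say which.

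Keeping withdrawn patients only when they already had an event is itself selection on outcome. Scoring the others event-free assumes the answer.

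**2. The plan's own figure.** Inputs from Sample size estimation: 55% against 30%, two-sided α 0.05, power 90%, chi-square test. With pooled variance (mean rate 0.425):

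n = [1.960·√(2·0.425·0.575) + 1.282·√(0.55·0.45 + 0.30·0.70)]² / 0.25² = 80.07, so 81 per group.

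Exact enumeration of the uncorrected chi-square test gives power 0.8997 at 81 and 0.904 at 82, so the stated 82 is reproduced. Inflating for loss gives 82/0.90 = 91.1, or 92 per group rather than 90. This is immaterial: 90 × 0.90 = 81 evaluable per arm still gives about 90% power.

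**3. Effect of outcome-linked loss.** If a share m of an arm with true event rate p is lost, and the lost patients have event risk q, the rate among those retained is

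p_obs = (p − m·q) / (1 − m).

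m = 0.10 is the plan's dropout allowance; q is assumed. For example, p = 0.55 and q = 0.80 give (0.55 − 0.08)/0.90 = 52.2%; q = 1 gives (0.55 − 0.10)/0.90 = 50.0%. Rejection probabilities are exact, with 81 analysed per arm. In each row, loss in the arm not named is unrelated to outcome.

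| Truth (standard / individualized) | Assumed risk among the lost | Observed rates | P(reject) |
|---|---|---|---|
| 55% / 55% | unrelated to outcome in both arms | 55.0% / 55.0% | 4.8% |
| 55% / 55% | individualized 80% | 55.0% / 52.2% | 6.3% |
| 55% / 55% | individualized 100% | 55.0% / 50.0% | 9.6% |
| 55% / 30% | unrelated to outcome in both arms | 55.0% / 30.0% | 90.0% |
| 55% / 30% | standard 80% | 52.2% / 30.0% | 82.2% |
| 55% / 30% | standard 100% | 50.0% / 30.0% | 73.9% |

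**4. Smaller losses.** With no true effect (55% in both arms), all losses in the individualized arm and every lost patient an event, type I error is 5.6% for 3 lost, 6.6% for 5 and 10.2% for 9.

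**5. Dropped or scored event-free.** With 90 patients at 55%, 49.5 events are expected. If 9 of these fall after withdrawal and go unseen, the rate is 40.5/81 = 50.0% when the patients are dropped and 40.5/90 = 45.0% when they are scored event-free. The choice the article leaves open therefore matters.

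**6. Sensitivity of a result at the planned effect.** Take 45/81 against 24/81 events, with 9 missing per arm. The complete-case P is 0.0008. If no missing standard patient had an event:
- 8 of 9 missing individualized patients with events: 45/90 against 32/90, P = 0.050.
- 9 of 9: 45/90 against 33/90, P = 0.071.

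These are extreme. With 9 of 9 individualized and 2 of 9 standard (47/90 against 33/90), P = 0.036; with 5 of 9 standard (50/90 against 33/90), P = 0.011.

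**The case against.** The strongest defence is that the plan loses fewer events than it first appears to. Data up to withdrawal are kept, so a patient withdrawn because of a qualifying dysfunction already counts. Assessment is daily, adjudication uses all data to day 7, and early discharges have a return visit or blinded telephone call. This stands, and it narrows the problem to patients withdrawn before a recorded event. It does not remove it: the return and telephone provisions are written for early discharge, and nothing extends them to patients withdrawn by the investigator.

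A second defence is that imputation and sensitivity analyses usually belong in a SAP, which is not shown. That also stands, and their absence is not the point here. The point is that the article fixes complete-case analysis for any missing data alongside a claim of intention-to-treat. A later SAP cannot recover outcomes that were never collected.

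A reader might also infer several stronger things that the documents do not support:
- *The bias favours the individualized arm.* If complications are commoner under standard care, as the trial hypothesises, withdrawal removes more standard-arm events and works against the intervention.
- *The person who withdraws patients is unblinded.* Only the anesthesiologist delivering the intervention is said to be unblinded. The principal investigator decides on withdrawal, and that person's blinding status is not stated.
- *Related SAEs fall mainly in the individualized arm.* Both arms can receive norepinephrine, so an imbalance is plausible but not established.
- *Deaths by day 7 escape the composite.* The definitions are in the S1 Appendix, which is not shown.
- *A doubling of type I error is to be expected.* That needs nine lost individualized-arm patients who all had events. The 10% is a general dropout allowance, not a forecast of withdrawals for complications.

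**Conclusion.** The point holds in this form. The stated rules do not amount to an analysis of all randomised patients: those withdrawn before a recorded event are dropped or scored event-free, the article does not say which, and the reasons for withdrawal can be linked to outcome and possibly to arm.

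Direction and size cannot be determined from the documents. At 10% loss per arm, type I error moves from about 5% to roughly 6–10% if the lost individualized-arm patients have 80–100% event risk. Power falls from 90% to 74–82% if the lost standard-arm patients do. With three to five lost events confined to the individualized arm, type I error stays at about 5.6–6.6%. The event risks among lost patients are assumptions; the 10%, 55% and 30% are the plan's. If loss is unrelated to outcome, neither error rate is disturbed.

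**What to change.** **Withdrawal criteria.** Separate stopping the allocated blood pressure strategy from leaving the study. State that day-7 and day-30 outcomes are collected for every randomised patient who has not withdrawn consent to follow-up, whatever the reason the strategy was stopped. Treat inability to complete the day-7 assessment as missing data, not as a reason for withdrawal.

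**Statistical analysis.** Analyse all randomised patients in their allocated arm. Keep counting any qualifying event recorded before withdrawal. Use multiple imputation for outcomes still missing, so that an incomplete window without an event is not scored event-free by default. Add a best/worst-case or tipping-point sensitivity analysis, and demote complete-case analysis to a sensitivity analysis.

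**Death.** If the S1 Appendix does not already do so, state how a death by day 7 without recorded organ dysfunction is counted.

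**Cost.** Wording changes, routine follow-up in a few more patients and a little more analysis work. The article reports recruitment as ongoing with completion planned for June 2026, so the follow-up change is the urgent part.

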## Discussion

This randomized controlled trial is designed to evaluate whether an individualized blood pressure management strategy (targeting SBP within ± 10% of baseline) can reduce postoperative organ dysfunction more effectively than a standard reactive management strategy in older patients undergoing hip fracture surgery under general anesthesia. The underlying mechanism is hypothesized to be through preemptive stabilization of hemodynamics, thereby minimizing exposure to IOH and maintaining personalized organ perfusion pressures tailored to individual autoregulatory thresholds.

The primary goals of anesthetic management in hip fracture patients are to mitigate postoperative complications and facilitate early recovery and functional rehabilitation [21]. IOH is a well-established, independent risk factor for a spectrum of adverse outcomes, including AKI, myocardial injury, and postoperative delirium [22, 23]. Notably, cardiovascular events and AKI are leading contributors to the high 30-day mortality observed after non-cardiac surgery, with up to one-third of deaths potentially attributable to perioperative myocardial injury [23]. Consequently, optimizing intraoperative hemodynamics is paramount for improving outcomes in this vulnerable geriatric population [24].

General anesthetic agents induce vasodilation and reduce systemic vascular resistance, compromising cardiovascular compensatory mechanisms [25]. This is particularly detrimental in older patients with diminished physiological reserve and impaired autoregulation. Evidence consistently demonstrates that blood pressure deviations exceeding 30% from baseline are associated with prolonged recovery and increased mortality [26, 27]. This underscores the limitations of a one-size-fits-all approach using fixed thresholds (e.g., MAP < 65 mmHg or SBP < 90 mmHg) and supports the rationale for individualized targets based on preoperative baseline values.

In the previous study, Futier et al. [15] demonstrated that individualized SBP management during major abdominal surgery reduced postoperative organ dysfunction. We hypothesize that an individualized perfusion pressure management strategy, guided by baseline blood pressure and initiated preemptively before hypotensive events, may improve tissue oxygenation and microcirculation in older hip fracture surgery patients, thus mitigating multi-system ischemic injury.

The choice of norepinephrine as the primary vasopressor is based on its favorable pharmacological profile for this population. Unlike phenylephrine, which is a pure α-agonist and can reduce heart rate and cardiac output, norepinephrine possesses both α- and β-adrenergic activity. Its β1-effects provide mild positive inotropy, supporting cardiac output, while its vasoconstrictive effects improve venous return. This profile facilitates a more stable elevation in blood pressure with less impact on heart rate compared to pure vasoconstrictors. Furthermore, compared to ephedrine, which exhibits tachyphylaxis and variable effects [28], a continuous low-dose infusion of norepinephrine offers more predictable and titratable control, making it ideally suited for preemptive stabilization [29]. While concerns exist regarding vasopressor use and renal perfusion [29], the protocol employs low doses aimed at preventing profound hypotension, which is a greater threat to renal autoregulation. Evidence from animal models suggests norepinephrine can effectively restore microcirculatory flow during hypotension without compromising gut oxygenation [30].

This study has several limitations. First, as a single-center trial, the generalizability of our findings may be limited. However, the single-center design enhances internal validity by standardizing the intervention and perioperative care. Second, in compliance with our institutional ethics committee guidelines, we excluded patients over 85 years of age. While this enhances safety for our initial investigation, it means our results may not be directly extrapolated to the very older population, who represent a significant proportion of hip fracture patients and may derive substantial benefit from such management strategies. Future research should specifically address this age group. Lastly, the composite primary outcome, while designed to capture the overall burden of organ dysfunction, may mask specific effects on individual organ systems. However, it provides a holistic measure of patient-centered morbidity.

Despite these limitations, this trial is poised to provide high-level evidence regarding the efficacy of individualized blood pressure management in reducing postoperative multi-organ dysfunction among geriatric hip fracture patients. Our findings are expected to contribute to the development of standardized, evidence-based clinical protocols aimed at optimizing perioperative outcomes and improving survival and functional recovery in this vulnerable population.

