**Discussion:**

This randomized controlled trial aims to determine whether individualized blood pressure management reduces postoperative organ dysfunction more effectively than standard management in older hip fracture surgery patients. If proven effective, this proactive approach may represent a significant advance in clinical practice, moving from reactive hypotension correction to preventive stabilization, potentially reducing major complications, shortening hospital stays, and improving functional recovery. The results will provide important evidence to guide hemodynamic management during general anesthesia in this vulnerable population, contributing to standardized, evidence-based protocols for enhancing perioperative outcomes.

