## Background

Hip fracture is a common and serious injury among older patients, associated with a one-year mortality rate as high as 30% [1]. Survivors often face long-term challenges, including multiple systemic complications, disability, increased risk of refracture, and substantial healthcare costs [2].

The anesthetic management of hip fracture surgery commonly involves either neuraxial or general anesthesia. While both are acceptable, general anesthesia is frequently preferred or necessitated in cases of patient agitation, anticoagulation, difficult positioning, or anticipated prolonged and complex surgery [3–5]. However, general anesthetic agents can induce significant arterial and venous vasodilation, reduce systemic vascular resistance, and cause hemodynamic instability [6]. These effects are compounded by the age-related impairment of cardiovascular autoregulation and a high prevalence of comorbidities, which collectively render older hip fracture patients particularly susceptible to intraoperative hypotension (IOH) [7].

IOH is a well-established risk factor for hypoperfusion of vital organs, leading to adverse outcomes such as postoperative delirium [8], acute kidney injury (AKI) [9, 10] and myocardial injury [11], ultimately worsening the prognosis. The prevalence of IOH in this population is high. A large UK study reported that 61.0% of older hip fracture patients experienced a mean arterial pressure (MAP) < 65 mmHg, and 91.3% had a reduction in systolic blood pressure (SBP) > 20% from baseline [12].

Despite its high prevalence and strong association with poor outcomes, there is no consensus on the optimal definition or management strategy for IOH. Current guidelines primarily recommend avoiding excessive hypotension (e.g., a > 30% decrease from baseline or an absolute SBP < 90 mmHg) and maintaining MAP ≥ 65 mmHg [13, 14]. This approach is inherently reactive, as treatment is initiated only after hypotension occurs. Furthermore, the fixed threshold of MAP ≥ 65 mmHg may not be optimal for all patients, as it fails to account for individual variations in baseline blood pressure and autoregulatory thresholds.

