In contrast to this reactive approach, an emerging paradigm is individualized or preemptive blood pressure management, which aims to maintain SBP within a narrow range (e.g., ± 10%) of baseline. This strategy has shown promise in reducing postoperative organ dysfunction in patients undergoing major abdominal surgery [15, 16], suggesting that proactive stabilization may be superior to reactive correction. However, high-quality evidence from randomized controlled trials is lacking specifically in older hip fracture patients.

Therefore, we hypothesize that an individualized blood pressure management strategy (targeting SBP within ± 10% of baseline) will reduce the incidence of postoperative organ dysfunction compared to a standard management strategy (preventing SBP < 90 mmHg or a decrease of > 30% from baseline) in older patients undergoing hip fracture repair under general anesthesia.

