### Anesthesia induction and intervention

After preoxygenation, general anesthesia will be induced with intravenous sufentanil (0.2–0.3 μg/kg), etomidate (0.1–0.2 mg/kg), and rocuronium (0.6 mg/kg). An i-gel supraglottic airway will be inserted, and mechanical ventilation will be commenced.

Hemodynamic management will begin immediately post-induction. In the individualized management group, a continuous peripheral intravenous infusion of norepinephrine (10 μg/mL) will be started at 0.02 μg/kg/min and titrated to maintain SBP within ± 10% of the baseline, with a maximum dose of 0.2 μg/kg/min. In the standard management group, intermittent intravenous boluses of norepinephrine (10 μg) will be administered as rescue therapy only if hypotension occurs (defined as SBP < 90 mmHg or a > 30% decrease from baseline). For all patients, the MAP will be maintained at ≥ 65 mmHg as a universal minimum target [17]. If target blood pressure cannot be maintained at the maximum dose, rescue therapy (e.g., dopamine 2–5 μg/kg/min or epinephrine 0.01–0.05 μg/kg/min) will be initiated based on real-time hemodynamic monitoring. Finally, an ultrasound-guided supra-inguinal fascia iliaca compartment block (S-FICB) with 35 mL of 0.25% ropivacaine will be performed on the surgical side for postoperative analgesia.

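### For a reference SBP below 100 mmHg the individualized target band reaches into what the article scores as hypotension; reference SBP is also absent from the named adjusted model

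*Protocol article*

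**What the plan says.** Under Anesthesia induction and intervention, the individualized arm receives a continuous norepinephrine infusion, begun right after induction and "titrated to maintain SBP within ± 10% of the baseline". The standard arm receives norepinephrine boluses as rescue, "only if hypotension occurs (defined as SBP < 90 mmHg or a > 30% decrease from baseline". Both arms share a MAP floor of 65 mmHg. The baseline is the reference SBP of the Preoperative interview section, the mean of three stable readings taken the day before surgery. The Exclusion criteria remove a resting SBP of 180 mmHg or more and set no lower SBP limit.

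The Secondary outcomes section defines intraoperative hypotension, for both arms, as SBP below 90 mmHg, a fall of more than 30% from baseline, or MAP below 65 mmHg.

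Statistical analysis compares the primary outcome by chi-square test and adds a "multivariable logistic regression model adjusting for age (as a continuous variable) and ASA physical status classification". A further secondary logistic model adjusts for baseline covariates that are not listed.

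On rationale, the Discussion states: "Evidence consistently demonstrates that blood pressure deviations exceeding 30% from baseline are associated with prolonged recovery and increased mortality". It takes this to show the "limitations of a one-size-fits-all approach using fixed thresholds". The Background makes a related remark, that "the fixed threshold of MAP ≥ 65 mmHg may not be optimal for all patients". The hypothesis, also in the Background, defines the comparator as "preventing SBP < 90 mmHg or a decrease of > 30% from baseline".

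**The concern.** The individualized target moves with the patient's baseline. The hypotension definition contains an absolute SBP limit that does not. At a low enough baseline the lower edge of the target band passes under that limit. A patient managed exactly as assigned then contributes a hypotension event, and the same pressure would prompt rescue in the standard arm. For that patient the intended direction of the contrast at the lower limit, with the individualized arm held higher, is reversed.

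At stake are the meaning of a secondary outcome in a few patients and the clarity of the contrast between arms. Two smaller matters follow from the same rules. Reference SBP anchors both strategies, yet it is not in the named adjusted model. And part of the Discussion's argument is aimed at a fixed-threshold rule that is not the comparator in this trial.

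**Working it through.** **Inputs.** R is the reference SBP (Preoperative interview). The individualized band is 0.9R to 1.1R, and the standard arm treats at SBP < 90 or a fall of more than 30% (both from Anesthesia induction and intervention). The hypotension outcome includes SBP < 90 (Secondary outcomes). Eligibility has an upper SBP bound of 180 only (Exclusion criteria).

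**The plan's own figure.** The article gives no figure for the separation between arms. Its one design figure, 82 per group for 55% versus 30%, is not in dispute: the pooled two-proportion formula without continuity correction gives 81. Nothing below changes it.

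**Target band against the hypotension limit.** The lower edge falls under 90 mmHg when 0.9R < 90, that is, R < 100.
- R = 95: 0.9 × 95 = 85.5 and 1.1 × 95 = 104.5. SBP from 85.5 up to just under 90 is on target and also counts as hypotension.
- R = 90: the band is 81 to 99, and the overlap runs from 81 up to 90.

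**Lower-limit gap between arms.** The standard arm's SBP floor is max(90, 0.7R). The relative part takes over when 0.7R > 90, that is, R > 90/0.7 = 128.6 mmHg. The gap is 0.9R − max(90, 0.7R).

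| R (mmHg) | Individualized lower edge | Standard floor | Gap |
|---|---|---|---|
| 95 | 85.5 | 90 | −4.5 |
| 100 | 90 | 90 | 0 |
| 110 | 99 | 90 | 9 |
| 120 | 108 | 90 | 18 |
| 130 | 117 | 91 | 26 |
| 150 | 135 | 105 | 30 |

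Above 128.6 mmHg the gap is 0.9R − 0.7R = 20% of R. This concerns the lower SBP limit only. At R = 100 the individualized arm still has an upper limit of 110 mmHg and an infusion running from induction, and the standard arm has neither.

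**How often R < 100.** The documents give no distribution. Assume a normal one cut at 180, so the share is Φ((100 − mean)/SD) / Φ((180 − mean)/SD).
- Mean 130, SD 18: Φ(−1.67)/Φ(2.78) = 0.0478/0.9973 = 4.8%, about 9 of 180.
- Mean 145, SD 20: Φ(−2.25)/Φ(1.75) = 0.0122/0.9599 = 1.3%, about 2 of 180.

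Mean 135 and mean 140, each with SD 20, give 4.1% and 2.3%. Across these four cases the median gap is 26 to 29 mmHg, and 71–89% of patients have a gap of at least 18 mmHg (R of 120 or more).

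**Rationale against comparator.** The Discussion moves from harm beyond a 30% deviation to the weakness of fixed limits and on to individualized targets. The standard arm already acts on a fall of more than 30% from the same baseline. The cited evidence therefore supports a rule that both arms respect, and does not by itself favour 10% over 30%. Separately, target width and drug delivery change together between the arms. The Discussion credits norepinephrine with mild inotropy and better venous return, and the continuous infusion with more predictable control. The stated limitations (single center, age cap, composite outcome) do not mention that these are tested as one package.

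**The case against.** The intervention section sets management by arm, and the Secondary outcomes section defines a descriptive variable for everyone, so one can say that they do different jobs and need not agree. The shared MAP floor may also prompt treatment in some patients with a low reference, whatever their SBP. Both remarks have force, and they keep the point small. They do not remove it: the MAP floor does not fix SBP, and a patient within the assigned SBP target can still be counted under the SBP < 90 criterion.

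On the model, randomization protects the unadjusted chi-square test. The unlisted covariates of the secondary logistic model, or an analysis plan not shown, may already include reference SBP. That stands, so its absence from the age and ASA model is an opportunity missed and not an error.

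On the wording, comparing two disclosed strategies that each bundle a target with a delivery mode is a legitimate design.

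A reader might infer more: that the trial is posed as individualized targets against fixed thresholds, that the SBP contrast vanishes near a reference of 100 mmHg, or that a null result could be put down to patients with almost no contrast. The documents do not support these readings. The abstract and hypothesis state the 30% criterion openly. The Background calls the usual approach reactive, and the abstract's discussion speaks of "moving from reactive hypotension correction to preventive stabilization". The closing claims do not say that individualized targets beat fixed ones. At 100 mmHg only the lower limits meet. Under the assumed distributions most patients have a wide gap, so the dilution argument is weak.

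**Conclusion.** The conflict between target and outcome definition is real for any reference SBP below 100 mmHg, by arithmetic on the article's own rules and the lack of a lower SBP limit in the eligibility criteria. Its size is small: roughly 2 to 9 of 180 patients, a range that rests wholly on the assumed mean and SD. It bears on a secondary outcome and on the direction of the lower-limit contrast in those patients. The primary endpoint, its test and the planned sample size are untouched. Adding reference SBP to the adjusted model is a free improvement. The mismatch between rationale and comparator, and the unmentioned bundling, are minor matters of wording.

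**What to change.** 1. Reconcile the individualized target (Anesthesia induction and intervention) with the hypotension definition (Secondary outcomes) for a reference SBP below 100 mmHg, and say how an on-target SBP under 90 mmHg is to be counted. Which rule should give way is a clinical decision, and no threshold is proposed here. Cost: a clarification.
2. Add reference SBP, as a continuous covariate, to the supplementary logistic model with age and ASA class, fixed before the analysts are unblinded. It is already measured before randomization, so the cost is one model term.
3. In the Discussion, note that the evidence on deviations beyond 30% supports a rule the standard arm already applies. Add to the limitations that the trial compares a tighter target with continuous infusion against rescue boluses, and cannot separate target from delivery. Cost: two sentences and a slightly narrower claim.

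An interaction of treatment with reference SBP, or a display split near 129 mmHg, is optional and exploratory only. With 180 patients it would be imprecise, and the split is crude because below it the gap runs from negative to nearly 26 mmHg.
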